***Randomization*:** Randomization will be performed after baseline assessment. Participants will be randomized to both arms equally a (1:1 ratio) upon final confirmation of eligibility. A stratified randomization will be performed by site and sex; with block size 2,4 and 6 to ensure unbiased allocation of the patients. Allocation to study group will be revealed using RedCap software to the research team that will carry out the intervention once baseline assessment is completed.

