### 3.6 Statistical analyses

#### 3.6.1 Sample size.

Sample size was calculated for the primary outcome of complications as defined by the CCI. From the literature, the mean CCI ranges from 25–35 after open AAA repair, and their standard deviations are 17–30. We have chosen 30 as the most clinically relevant mean difference for the CCI and standard deviation of 20. Given the inputs, we require a total of 126 patients to achieve standard 80% statistical power and 5% tolerance. After considering a 20% dropout rate, we require 152 patients (76 per group) in this study. Since one interim analysis was planned, a total of 40 patients were needed in each treatment arm at the time of analysis to adequately power the interim analysis based on the type-I error suggested by the O’Brien-Fleming method (a minimum P = 0.0054).

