#### 3.6.3 Interim analysis.

An interim analysis will be conducted at the halfway (when we reach half the numbers) point of recruitment to assess the safety and the primary outcome endpoints. An independent statistician will perform the analyses, and the data safety monitoring committee will determine the results and decide about the trial’s continuation as designed.

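### The 40 per arm said to power the interim analysis does not follow from the plan's own inputs, and it disagrees with the halfway-of-recruitment trigger

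*Protocol article*

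**What the plan says.** Section 3.6.1 (Sample size) gives these inputs: "We have chosen 30 as the most clinically relevant mean difference for the CCI and standard deviation of 20". From them it derives the total: "we require a total of 126 patients to achieve standard 80% statistical power and 5% tolerance". Dropout then raises it: "After considering a 20% dropout rate, we require 152 patients (76 per group) in this study". For the single planned interim analysis it says that "a total of 40 patients were needed in each treatment arm at the time of analysis to adequately power the interim analysis", at a type I error attributed to the O'Brien-Fleming method (P = 0.0054).

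Section 3.6.3 (Interim analysis) sets the timing: "An interim analysis will be conducted at the halfway (when we reach half the numbers) point of recruitment". That look covers safety and the primary outcome, and the committee then decides whether the trial continues as designed.

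Section 3.6.2 assesses the CCI at 45 days. Section 3.5.4 puts 6 ± 1 weeks of prehabilitation before surgery. Section 3.5.2 randomises 1:1.

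**The concern.** A reader, or a monitoring committee, would take section 3.6.1 to mean that the interim test has a good chance of detecting the effect for which the trial is sized. For the effect that yields 126, the chance is under one in three. A non-significant interim would then be the expected result even if the programme works as planned, and it would say little about efficacy.

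The two sections also leave open how many patients are in the look. That number fixes the information fraction, and the O'Brien-Fleming levels depend on it.

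**Working it through.** **Inputs.** From section 3.6.1: difference 30 as written, SD 20, 80% power, 5%, 126 evaluable, 152 randomised (76 per arm), interim 40 per arm at 0.0054. From section 3.5.2: 1:1 allocation. Assumption: two-sided tests, since sidedness is not stated.

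**Step 1. Reproduce 126.** Per arm, n = 2·SD²·(z₁ + z₂)²/Δ², with z₁ = 1.960 and z₂ = 0.842.
- Δ = 30: 800 × 7.849/900 = 6.98, so 7 per arm (14 in total). This is not 126.
- Δ = 10: 800 × 7.849/100 = 62.8, so 63 per arm (126 in total). This is the plan's figure.

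Solving back from 63 per arm gives Δ = 9.98. The document never states 10 points. It is inferred from 126.

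**Step 2. Power at 40 per arm and 0.0054.** The critical value is z = 2.782. The standard error is 20·√(2/40) = 4.47.
- Difference needed to cross: 2.782 × 4.47 = 12.4 points.
- Δ = 10: 10/4.47 = 2.236, and Φ(2.236 − 2.782) = Φ(−0.546) = 0.29. With the t distribution it is 0.27.
- Δ = 30: power is above 99.9%.
- Over the quoted SD range of 17 to 30, power for 10 points runs from 44% down to 10%.

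**Step 3. Patients needed for 80% power at 0.0054.** Here (2.782 + 0.842)² = 13.13.

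| Difference | n per arm (normal) | n per arm (t) | Plan |
|---|---|---|---|
| 10 | 105.05, so 106 | 108 | 40 |
| 30 | 11.7, so 12 | 14 | 40 |

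For 10 points, even all 76 per arm would give only Φ(3.082 − 2.782) = 62% at this level. At 40 per arm, 80% power corresponds to 3.624 × 4.47 = 16.2 points, a value the document does not mention.

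**Step 4. Timing.** Half of 152 is 76, or 38 per arm. Half of 126 is 63, or about 32 per arm. Section 3.6.1 has 80 in total, which is 52.6% of 152 and 63.5% of 126. The classical two-look O'Brien-Fleming levels move with the fraction:

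| Information fraction | Interim level | Final level |
|---|---|---|
| 50% | 0.0052 | 0.0480 |
| 52.6% (80/152) | 0.0063 | 0.0476 |
| 63.5% (80/126) | 0.0122 | 0.0457 |

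At the last row, z = 2.507 and power for 10 points at 40 per arm is Φ(2.236 − 2.507) = 39%. This is still far from 80%.

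**Step 5. Recruits versus outcomes.** A recruit's CCI is not known until prehabilitation, surgery and the 45-day period are over. As an illustration only, assume even accrual over 36 months (152/36 = 4.2 a month), surgery straight after week 6, the 45 days counted from surgery, and data cut at the trigger. The lag is 42 + 45 = 87 days, about 2.9 months, so about 12 of the first 76 recruits would lack a CCI. That leaves about 32 per arm before dropout. There the standard error is 5.0, and power for 10 points is Φ(2.000 − 2.782) = 22%.

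**The case against.** The strongest reply is that the document states a difference of 30, not 10. On that figure 40 per arm gives almost certain detection, so the interim is more than adequately powered. It follows that 28% cannot be asserted unconditionally. The reply does not rescue the plan, though. With 30 points, 40 per arm are not needed and 126 is wrong. It is also hard to credit as a target, since the section reports that "the mean CCI ranges from 25–35 after open AAA repair, and their standard deviations are 17–30", so a 30-point difference would remove nearly the whole complication burden. The interim problem is largely a consequence of that sample-size error.

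On timing, 40 against 38 per arm is only four patients in total. The wording of section 3.6.1 can also be read as patients with data in hand. If so, 80 evaluable patients need 80 × 1.2 = 96 to 80/0.8 = 100 randomised, which is 63–66% of 152. The disagreement with half of recruitment then widens.

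Three stronger readings are tempting but not supported:

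- **Final test at an unreduced 5%.** The only 5% given is the sample-size input ("to achieve standard 80% statistical power and 5% tolerance"). No final test level is stated, O'Brien-Fleming itself supplies one, and an article may leave it to the analysis plan. Even a full 0.05 after 0.0054 at half information would give an overall error of about 5.2%.
- **0.0054 as an error.** At half information the classical level is 0.0052. The gap is immaterial, and comparing it with the level from a spending function would substitute a variant that the protocol does not name.
- **A null interim would stop the trial.** No futility rule is stated, so this is speculation.

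**Conclusion.** The point holds in a limited form. The statement that 40 per arm are needed to power the interim follows from neither reading of the inputs. For the 10 points that reproduce 126, power is about 27–29%, and 80% would take 106 per arm, more than the trial plans to randomise. For 30 points, about 12 per arm suffice. The power figure is conditional on the inferred 10 points, SD 20 and a two-sided test.

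Sections 3.6.1 and 3.6.3 also disagree on the size of the look: 40 per arm against 38 or about 32. A recruitment trigger yields fewer completed CCIs than the number recruited. How many fewer depends on accrual, waiting time for surgery and dropout, so the figure of 12 is only illustrative. Nothing here shows that the type I error is lost. The correction is worth making because the document asserts a property that the interim does not have.

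**What to change.** 1. In section 3.6.1, correct the difference so that it agrees with 126. Delete the claim of adequate power and state the interim's actual operating characteristics. If the difference is 10 points with SD 20, these are about 28% power at 40 per arm and 0.0054, with crossing at an observed difference of about 12.4 points.
2. Give one trigger in sections 3.6.1 and 3.6.3, defined as a fixed number of patients with a completed 45-day CCI. For example, 63 would be half of 126, and 80 would keep 40 per arm.
3. Take the O'Brien-Fleming interim level and its matching final level from the actual information fraction, measured against the planned number of evaluable patients. At half information the final level is about 0.048. Sizing for 10 points at that level raises 63 per arm to 64.

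The cost is wording in the two sections and matching text for the monitoring board. The look will come some months later than a recruitment trigger, by an amount that depends on accrual and dropout.

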#### 3.6.2 Primary analysis.

The primary analysis will be conducted by the intent-to-treat approach; differences in CCI scores between MP and the standard-of-care arms will be assessed in 45 days. Descriptive statistics will be performed using means, proportions, medians, standard deviations, and interquartile ranges, as appropriate depending on the nature of the data. We will use Generalized Linear Mixed or Generalized Estimation Equation models to evaluate the impact of the intervention, accounting for between and within group differences. The effect of MP on specific postoperative complications will be analyzed using parametric tests for categorical variables. The effect of MP on functional improvement and quality of life will be analyzed using time interactions with the group after considering the site at a random level. In addition, we will perform the sensitivity analysis based on a per-protocol approach using mixed effects, with study site as the random effect to cross-validate our results. We also plan to perform subgroup analyses of the primary outcome measure, as well as MP adherence on the following groups: study site, sex, and other variables which have previously been shown to impact MP adherence as well as postoperative outcomes after AAA repair, such as age, diabetes, renal failure, and baseline functional status.

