### 3.4 Study outcomes

#### 3.4.1 Primary outcome.

The primary outcome of this study is the incidence of postoperative complications measured by the Comprehensive Complication Index. The CCI was developed to address some of the limitations of traditional surgical morbidity reporting, such as only reporting the most severe complication or only picking the most common types of complications [55,56]. It provides a continuous score from 0 (no complications) to 100 (death) that integrates the cumulative burden of all complications and their severity. It has been validated in surgical abdominal, urologic, and cardiothoracic patient populations [47,57,58]. It correlates better than any other scale with respect to length of stay, cost/burden to the health care system, readmissions, and disability [59–61].

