#### 3.4.2 Secondary outcomes.

Secondary outcome measures will fall into 5 categories:

Healthcare-related: Intraoperative complications, ICU length of stay, hospital length of stay, reintervention, 6-week and 1-year mortality/ readmission/ emergency room visit and prehabilitation cost-effectiveness.Change in functional and aerobic capacity measured by:6-minute walk test: the 6MWT evaluates the ability of an individual to maintain a moderate level of physical activity reflective of the activities of daily living [62]. As daily activity is mostly pursued at a submaximal level, functional walking capacity is a more direct measure of capacity for daily routine. Therefore, it is a useful tool to assess postoperative recovery and return to normal life [63].VO2-peak, VO2-AT, VE/VCO2-AT: Cardiopulmonary Exercise Testing (CPET) is the current gold standard to assess aerobic capacity [64]. It provides an assessment of the integrative exercise responses involving the pulmonary, cardiovascular, hematopoietic, and skeletal muscle systems [64]. VO2 peak, VO2-AT and VE/VCO2-AT are CPET derived variables that predict postoperative morbidity and mortality, as well as indicators of cardiorespiratory fitness.Yale physical activity survey (YPAS): YPAS is a self-reported measure of physical activity, comprising 18 activities evaluated according to the total number of hours done during an average week [65].Patient reported outcomes:Health-related quality of life (SF-36): the SF-36 is the most widely used health-related quality of life measure and has been validated for surgical populations. It incorporates behavioral functioning, subjective wellbeing, and perceptions of health. Two summary scores have been developed: the Physical Component Summary and the Mental Component Summary, standardized to have a mean of 50 and a standard deviation of 10. A higher score on the SF-36 sub-scales or component summary measures indicates a better quality of life. A change of as little as 2 units on the physical component summary has been shown to be the minimum clinically meaningful change; 5 points is often targeted by medical intervention studies, though surgical interventions can have an impact as large as 10 points [66,67]. Data obtained from the SF-36 will be used to calculate the quality adjusted life years using the SF-6D [66].Hospital Anxiety and Depression Scale (HADS): HADS is a reliable instrument for screening clinically significant anxiety and depressive symptoms in medically ill patients [68]. It has also been shown to be a valid measure of their severity [68]. It includes items that assess generalized depression and anxiety, including tension, worry, fear, panic, difficulties in relaxing, and restlessness.Nutritional status outcomesPatient Generated Subjective Global Assessment (PGSGA): the PGSGA is a screening tool used to identify malnutrition and consists of two parts. The first part is the Patient Generated Subjective Global Assessment Short Form which is a widely validated malnutrition screening tool and has been previously used in vascular surgery [69–71]. The second part is completed by a dietitian and includes a physical examination, where fat and muscle stores and fluid status are evaluated, and an assessment of the disease/condition. The global score generates a subjective category rating for nutritional status.Body composition: Weight, BMI, Fat free mass (kg) and body fat mass (%) will be assessed using bioimpedance.Diet: A registered dietitian will assess usual energy and protein intake, including supplements, at baseline and pre-surgery using three-day food records or 24-hour dietary recalls.Study related outcomes:Compliance: compliance to supervised and home-based exercise will be calculated by counting the number of sessions attended by the participant. Home-based exercise compliance will be estimated by counting the number of sessions they logged in an exercise logbook. Compliance to nutrition will be evaluated based on the assessment of dietary changes/goals set by the dietitian. Every week participants will be asked if the nutrition goals set have been met.Fidelity: fidelity to supervised and home-based exercise will be recorded. Supervised exercise fidelity will be measured by recording the watts (for endurance training) and kg (for strength training) at which the participants train during the session (versus expected according to the individualized plan) as well as heart rate and RPE for both breathing and muscular fatigue [72].Satisfaction and acceptability of the intervention: a satisfaction survey enquiring about the different components of the prehabilitation will be given upon completion of the intervention (S1 File).Safety: safety will be assessed by recording the appearance of any adverse event occurring during assessments or intervention. A list of adverse events can be found in S5 File.

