#### 3.5.6 Surgery and admission (T8).

Perioperative clinical protocols will be followed according to each site’s standard of practice independently of group allocation; [76]. Anesthesia procedures and surgery will be performed by the usual anesthesia and vascular surgery teams of each site. Hospital healthcare providers (nurses, anesthesiologist, vascular surgeons, physiotherapists, etc.) involved in the participants care will be blinded to the study group allocation, unless the participant discloses that information. To avoid that, participants will be advised not to disclose their allocation to healthcare providers. Any intraoperative deviation of the standard course or event will be recorded (S3 File). The use of blood products, as well as the need for high doses of vasopressors intraoperatively will also be recorded (high doses of one vasopressor or the use of two or more vasopressors) in the case report form. Postoperative care will not differ between groups and will follow the standard of practice for each site. Postoperative complications throughout admission will be assessed daily by a physician and will be recorded in the CRF by a research team member. Both team members will be blinded to the study group allocation to avoid bias. The primary outcome of the study, the Comprehensive Complication Index (CCI), will be calculated based on the number and severity of the complications recorded. A description of complications and their severity can be found in the S4 File. Length of ICU stay, need for a reintervention and hospital length of stay will be recorded.

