#### 3.5.7 Postoperative assessment (T9).

Six weeks after discharge, participants will undergo a postoperative assessment where the following measurements will be performed:

Resting blood pressure, heart rate and oxygen saturation.6-Minute Walk TestYale Physical Activity SurveySF-36 V.2 questionnaireHADs questionnaire

Emergency room visits and readmissions, from discharge to postoperative assessment, will also be assessed and recorded.

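### The primary CCI is built from complications recorded during the admission but compared over 45 days with no stated day 0, so the primary endpoint has two windows that need to be reconciled

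*Protocol article*

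**What the plan says.** Four sections of the protocol article bear on the window of the primary outcome.

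- **Definition (3.4.1).** "The primary outcome of this study is the incidence of postoperative complications measured by the Comprehensive Complication Index". The scale runs from 0 to 100, with 100 for death. No start or end of observation is given.
- **Collection (3.5.6, T8).** "Postoperative complications throughout admission will be assessed daily by a physician and will be recorded in the CRF by a research team member". The CCI "will be calculated based on the number and severity of the complications recorded".
- **Analysis (3.6.2).** "differences in CCI scores between MP and the standard-of-care arms will be assessed in 45 days". Day 0 is not named.
- **Next visit (3.5.7, T9).** "Six weeks after discharge, participants will undergo a postoperative assessment". The visit lists vital signs, the walk test and three questionnaires, and adds: "Emergency room visits and readmissions, from discharge to postoperative assessment, will also be assessed and recorded". Recording or grading of complications is not listed.

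Section 3.4.2 places "6-week and 1-year mortality/ readmission/ emergency room visit" among the secondary outcomes. The only other mention of 45 days is in section 3.6.4, for a resource-use questionnaire in the cost analysis.

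**The concern.** The collection rule as described does not deliver the endpoint that the analysis section names. A score built from complications seen during an admission is an in-hospital score of variable duration. A 45-day score needs ascertainment up to day 45 wherever the patient is. If the choice between them is left open, it could be made after data are known, and the interim look in section 3.6.3 already uses the primary endpoint.

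The admission window raises a second issue. It closes at discharge, which happens after randomization and may be affected by treatment. Length of stay is a secondary outcome, and section 3.7 expects the prehabilitation arm to recover faster. If that arm goes home sooner, it is observed for less time, and part of a lower CCI could reflect shorter observation.

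**Working it through.** The plan gives no figure for this point, so there is none to reproduce. The check compares the sections and then sizes the gap.

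**1. Can the windows coincide?** The admission window runs from surgery to discharge. If day 0 is surgery, it equals the 45-day window only for a patient who stays exactly 45 days. Shorter stays leave days without described complication recording. Longer stays carry recording past day 45.

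**2. Which day 0 is possible?**
- Surgery: T9 falls on day (stay + 42). This equals day 45 only for a 3-day stay.
- Discharge: day 45 falls 45 − 42 = 3 days after the nominal T9.
- Randomization: the programme lasts 6 ± 1 weeks, or 35 to 49 days, so day 45 would fall around the time of surgery. This origin makes little sense for postoperative complications.

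**3. Size of the gap with day 0 = surgery.** The documents give no length of stay, so the stays below are assumptions. Uncovered days = 45 − stay; T9 day = stay + 42.

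| Assumed stay (days) | Days of 45 without described recording | T9, day after surgery |
|---|---|---|
| 5 | 40 | 47 |
| 7 | 38 | 49 |
| 10 | 35 | 52 |
| 14 | 31 | 56 |
| 21 | 24 | 63 |
| 30 | 15 | 72 |

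For stays of 7 to 10 days, the admission covers 7/45 = 16% to 10/45 = 22% of the period. For all stays in the table, T9 falls after day 45, so an existing visit could close a 45-day window.

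**4. Do the windows change a score?** Two hypothetical patients show that they can, in either direction.
- Discharged without complications, dies on day 20 after surgery: 0 in the admission window, 100 in a 45-day window from surgery. One such patient shifts the mean of a 76-patient arm by 100/76 = 1.3 points.
- Stays 60 days, with a complication on day 50: counted in the admission window, not counted in a 45-day window from surgery.

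**5. Observation time and stay (illustration only).** If one arm's stay were 2 days shorter (assumed) than a stay of 7 to 10 days (assumed), its observed days would fall by 2/7 = 29% to 2/10 = 20%. This is a change in days observed, not in the CCI.

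**The case against.** A reader might infer that complications are recorded only in hospital and that later ones are lost. The documents do not support that. Section 3.5.6 describes what happens at T8 and does not say that recording stops at discharge. The 45-day wording suggests that the authors intend something longer. The schedule and study-flow figures (Figs 1 and 3) both define CCI in their captions, but their content is not shown, and S4 File, which describes complications and their severity, is not shown either. Any of these may hold a later CCI time point. T9 also records emergency visits and readmissions, and section 3.5.8 adds a records review at one year, so serious late events would probably leave a trace. What stands is narrower: no section shown says that those events are graded and enter the CCI, and sections 3.5.6 and 3.6.2 need aligning even if a figure settles the matter.

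A reader might also take the 20% to 29% as bias. It is not. It rests on two assumed figures, and it would carry over to the outcome only if risk were even across the stay. The days removed are the last before discharge, when patients are judged fit to leave. Complications also lengthen stay, so part of any difference in stay would be a consequence of the outcome.

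Finally, an in-hospital CCI is a legitimate endpoint that would also remove the contradiction. A longer window has drawbacks of its own: it relies on T9 attendance, with 20% dropout already assumed, and on reports from participants who know their allocation.

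**Conclusion.** The point holds as a contradiction about the primary endpoint. The score is calculated from complications recorded through the admission, compared over 45 days with no origin, and defined with no window. It goes beyond detail that a journal article may leave out, because the two stated windows can give the same patient different primary scores, by up to the full 100 points where a death occurs after discharge and before day 45.

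An admission-only window would also make observation time depend on length of stay, which the intervention may change. Whether this biases the comparison, in which direction and by how much cannot be determined from the documents. The uncovered-day counts assume that day 0 is surgery and use assumed stays. The conclusion is confined to the text shown; the figures and S4 File could show that later events are scored, but the sections would still disagree.

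**What to change.** Before the interim analysis, state one CCI window and its day 0 in sections 3.4.1, 3.5.6 and 3.6.2.

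- **Preferred.** All complications from surgery to day 45 after surgery, in or out of hospital. Add a graded complication form at the existing T9 visit, completed from readmission, emergency and clinic records and scored by the blinded assessors. Count only events up to day 45. Keep the in-hospital CCI as a supporting analysis.
- **Alternative.** Define the primary endpoint as in-hospital CCI, delete the 45-day wording from section 3.6.2, and acknowledge that observation time depends on length of stay.

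The preferred option costs one CRF page, a protocol and registry amendment (recruitment began in September 2024), and chart review for participants already past T9. It also brings some reliance on T9 attendance and on reports from unblinded participants; working mainly from records limits this. The alternative needs only the amendment, but keeps the dependence on stay.

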### 3.2 Setting

This trial will be conducted in the following academic tertiary hospitals: McGill University Health Centre (Montreal, Canada), Sir Mortimer B. Davis Jewish General Hospital (Montreal, Canada), Hospital Clínic de Barcelona (Barcelona, Spain) and Dalhousie University affiliated Hospitals (Nova Scotia, Canada).

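### The primary CCI model is left as a choice between GLMM and GEE with no clustering unit fixed; one permitted version, GEE clustered on site, would reject a true null in about 18–22% of trials instead of 5%

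*Protocol article*

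**What the plan says.** Section 3.6.2 gives the timing of the primary comparison, "differences in CCI scores between MP and the standard-of-care arms will be assessed in 45 days", and then the model: "We will use Generalized Linear Mixed or Generalized Estimation Equation models to evaluate the impact of the intervention". It gives no rule for choosing between the families and, for the primary endpoint, no clustering unit, variance estimator or covariate list.

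Section 3.4.1 describes the endpoint: "It provides a continuous score from 0 (no complications) to 100 (death) that integrates the cumulative burden of all complications and their severity". That is one number per patient; no repeated CCI measurement is described.

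Site appears elsewhere in 3.6.2. It is placed at the random level for the functional and quality-of-life outcomes, and the per-protocol sensitivity analysis is to be done "using mixed effects, with study site as the random effect to cross-validate our results". Sex appears there only as a subgroup variable.

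Section 3.5.2 sets the allocation: "A stratified randomization will be performed by site and sex; with block size 2,4 and 6". Section 3.2 lists four site entries. The last is plural (the hospitals affiliated with Dalhousie University), so the number of hospitals may exceed four. Section 3.6.1 sizes the trial at 80% power and a 5% error level.

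**The concern.** GLMM and GEE are methods for correlated observations. With one CCI per patient there is no within-patient correlation to model, so the grouping that 3.6.2 itself suggests is site. A GEE robust variance relies on many independent clusters, and four is far too few: the standard error comes out too small and the test rejects too often.

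Two things are at stake. One analysis that the text permits may not hold the 5% level on which the trial was sized. And because the options give different standard errors for the same data, leaving the choice open allows it to be made after results are seen, in a trial described in section 3.1 as open label. The primary outcome is also tested at the interim analysis (3.6.3), so the open choice affects two looks.

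**Working it through.** **Benchmark.** The article gives no error rate for its model beyond the 5% level in 3.6.1, so 5% is the figure to compare against.

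**Inputs.** From the article: 152 patients, 1:1 allocation, SD 20, four site entries, stratification by site and sex with blocks of 2, 4 and 6. Assumed: site sizes, between-site SD (for example 3 or 6 CCI points), 20% women, and a two-sided test.

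**Step 1: closed form for equal sites.** Take K sites of equal size, balanced 1:1 within each, and let d_k be the treated-minus-control mean difference in site k.

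- The estimate is the mean of the d_k, written d̄. Site effects cancel within each d_k.
- The uncorrected site-clustered sandwich variance is Σ(d_k − d̄)² / K².
- The ordinary variance of a mean of K values is Σ(d_k − d̄)² / [K(K − 1)].
- So z = t × √[K/(K − 1)], where t follows Student's t on K − 1 degrees of freedom (normal data).
- Rejecting at |z| > 1.96 is the same as |t| > 1.96 × √[(K − 1)/K].

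| Clusters K | Threshold on t | Closed-form null rejection | Simulated (10,000 trials) |
|---|---|---|---|
| 4 | 1.96 × √(3/4) = 1.697 | 18.8% | 18.6% |
| 5 | 1.96 × √(4/5) = 1.753 | 15.5% | 15.9% |
| 6 | 1.96 × √(5/6) = 1.789 | 13.4% | 13.6% |
| 8 | 1.96 × √(7/8) = 1.833 | 10.9% | 10.8% |

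With a t reference on 3 degrees of freedom the critical value is 3.182. The threshold becomes 3.182 × √(3/4) = 2.756 and the rejection rate 7.0%.

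**Step 2: simulation under the null, four sites, nominal 5%.**

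| Analysis | Null rejection |
|---|---|
| Site-clustered GEE, uncorrected sandwich, normal reference: equal sites | 18.6–19.4% |
| Same, moderately unequal sites | 19.6–20.6% |
| Same, strongly unequal sites (76/40/24/12) | 21.6–24.3% |
| Same, skewed data with many zeros | 18.6% |
| Same, t reference on 3 df | 6.5–9.2% |
| Site-clustered GEE, bias-reduced sandwich | 9.9–12.6% |
| GEE with the patient as cluster | 4.5–5.7% |
| Mixed model, random site intercept | 5–7% |
| Linear model, fixed site | 4.5–5.4% |

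The mixed-model row rests on 400 trials per scenario, with many convergence warnings. Its simulation standard error is about √(0.05 × 0.95/400) = 1.1 percentage points.

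A separate simulation with the actual blocks within site and sex, and 2,000 trials per scenario, gave 18.3–20.8% for site-clustered GEE (exchangeable working correlation), 4.1–5.6% for a linear model with fixed site and sex, and 4.0–5.3% for an unadjusted t-test.

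**Step 3: does leaving out sex matter?** Power was examined at a difference of 10, the value that reproduces the article's 126: 2 × (1.960 + 0.842)² × 20²/10² = 62.8, so 63 per arm. (The difference of 30 printed in 3.6.1 does not give 126; that is a separate matter.) For assumed sex effects of 0 to 10 CCI points, a fixed-site model gave:

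- without sex: type I error 4.6–5.1%, power 85–87%;
- with sex: type I error 4.6–5.2%, power 86–87%.

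**The case against.** The strongest reply is that the inflated rate belongs to an analysis the article never specifies. It needs site as the cluster, an uncorrected sandwich, a normal reference and only four clusters. Changing any one of these lowers the rate, and with the patient as cluster GEE is simply a regression with robust errors that holds about 5%. The mixed-model option is also broadly acceptable. The sentence may be meant generally, since 3.6.2 also covers repeated outcomes for which these methods suit. And an analysis plan, not shown here, would normally settle such details.

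Most of this stands, and it limits the point. A reader might infer that the planned primary test has a 20% false-positive rate; the text does not support that, because it commits to none of the conditions. A reader might also infer that the primary model omits sex and so wastes precision. The article lists no covariates for this model, which is silence rather than exclusion, and step 3 shows that leaving sex out costs almost nothing.

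What the reply does not remove is the open choice itself. It is printed under the primary-analysis heading, and site is the grouping that the same section uses in its other models. More hospitals (five to eight clusters) or a bias-reduced sandwich still leave about 10–16%. An analysis plan may close the choice, but the protocol as written does not.

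**Conclusion.** The point holds in a conditional form. The article fixes neither the estimator nor the clustering unit for a score measured once per patient, and the permitted versions differ materially in type I error. Site-clustered GEE with an uncorrected sandwich and normal reference gives about 18–22% with four sites, up to 24% if one site recruits half the patients. Patient-level robust or fixed-site linear models give about 5%, and a random-site mixed model 5–7%.

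The figures assume 1:1 balance within site, a two-sided 5% test and a constant treatment effect of zero. They depend little on between-site variance, which cancels in the within-site differences, or on skewness. The number of clusters is uncertain because of the plural last entry in section 3.2. This is a specification gap that should be closed before outcome data are seen; it does not show that the trial will be analysed wrongly.

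**What to change.** Replace the open choice in 3.6.2 with one named primary analysis: a linear model of the 45-day CCI on treatment, with fixed effects for the randomisation strata (site and sex), reporting the adjusted mean difference and its 95% confidence interval with patient-level heteroscedasticity-robust (for example HC3) standard errors. State that GEE clustered on site will not be used for this endpoint, and define site as the unit used in the randomisation, so that the Dalhousie entry is unambiguous. Apply the same model at the interim look. GLMM or GEE can remain for the functional and quality-of-life outcomes, where patients are measured repeatedly.

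Pre-specified baseline covariates and a permutation test within strata, as a check against skewness, are optional.

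The cost is a wording change and, with four sites, 3 + 1 = 4 degrees of freedom for site and sex.
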